## Abstract

**Background:**

Stroke causes functional decline, psychological disorders and cognitive impairments that affect activities of daily living and quality of life. Although physical activity (PA) is beneficial in stroke recovery, PA recommendations are rarely met after hospital discharge. There is presently no standard strategy for monitoring and inciting PA at home during the subacute phase of stroke recovery. The main aim of this study is to evaluate the effects of a home-based physical activity incentive and education program (Ticaa’dom) on functional capacity in subacute stroke patients.

**Methods:**

This study is a comparative prospective, observer-blinded, monocentric, parallel, randomized controlled clinical trial. This study will include 84 patients: 42 patients in the home-based physical activity incentive group (HB-PAI) and 42 in the control group (CG). The intervention group will follow the HB-PAI program over 6 months: their PA will be monitored with an accelerometer during the day at home while they record their subjective perception of PA on a chart; they will observe a weekly telephone call and a home visit every three weeks. The CG will receive traditional medical care over 12 months. The main study outcome will be the distance on a 6-minute walk test. Secondary outcomes will include measurements of lower limb strength, independence level, body composition, cardiac analysis, fatigue and depression state.

**Discussion:**

The results of this trial will demonstrate the value of implementing the Ticaa’dom program during the subacute phase of stroke recovery.

**Trial registration:**

ClinicalTrials.gov, NCT01822938. Registered on 25 March 2013.

**Electronic supplementary material:**

The online version of this article (doi:10.1186/s13063-017-2410-9) contains supplementary material, which is available to authorized users.

## Background

Strokes are experienced by almost 1.1 million people annually in Europe and cause approximately 1 in 19 casualties in the USA [1, 2]. Stroke patients commonly experience physical and cognitive impairments that affect activities of daily living (ADL), and contribute to sedentary lifestyles [3, 4]. Compared to their healthy peers, stroke survivors are less active, spend less time standing and walking [5], and engage in longer periods of uninterrupted sitting during the daytime [6]. However, physical activity (PA) and exercise are beneficial in all phases of stroke recovery [7, 8] and reportedly reduce cardiovascular risk factors [9, 10] while improving functional capacity and quality of life [11].

Systematic literature reviews reveal that stroke survivors receive an average of 2–6 days of PA monitoring after hospital discharge, and 3–6 months of home-based follow up [12–14]. The stroke population has a mean total energy expenditure (TEE) of around 321 kcal/day and a step count (SC) of 4355 steps/day, which is lower than the expected SC for people with chronic disability, i.e. 6500–8500 steps/day [13, 15]. Patients in the subacute phase of stroke recovery have significantly lower SC and spend more time in therapy and performing moderate activities compared to patients in chronic stroke recovery [16]. In this population, 30 minutes of cycle ergometer 3 days a week appears to be a sufficient amount of PA to increase peak oxygen uptake (VO_2_) and functional capacity and to improve the distance walked during a 6-minute walk test (6MWT).

Stroke patients often do not meet PA recommendations, i.e. at least 150 min a week of aerobic-moderate PA or 75 min a week of aerobic-vigorous PA [7]. Although there is no definite optimal strategy to encourage PA during subacute stroke recovery, potential approaches include home-based PA rehabilitation, structured rehabilitation exercises and secondary prevention programs [17–19].

On the subject of home-based PA in the subacute phase of stroke recovery, Studenski et al. [20] compared the motor control, balance, endurance and mobility of the upper and lower extremities following a 12-week cycle ergometer program. Compared to usual care, the intervention brought about better gains (*P* = 0.0056), in the form of improved scores in the Barthel Index (BI) and Balance Berg Scale (BBS), better peak aerobic capacity, improvements in the up-and-go test (TUG) and 6MWT, and better physical and social scores in the medical outcomes of the Short-Form 36-item (SF-36) questionnaire, better strength and improved upper extremity skills in subscales of the Stroke Impact Scale (SIS) and in quality of life (QOL) [20, 21].

To our knowledge, no study has yet investigated the effects of home-based PA incentive programs outside of standard and structured therapy during the subacute phase of stroke recovery. The investigated home-based PA incentive program (Ticaa´dom) could be a useful strategy to increase daily PA, to change sedentary lifestyle over time, and to establish PA monitoring after stroke. The primary aim of this planned study is to evaluate how a 6MWT is affected by the Ticaa´dom program over 12 months in the subacute phase of stroke recovery. We hypothesize that the PA incentive program will increase daily PA and independence among stroke patients. The secondary objective is to evaluate whether and how well patients keep practicing PA at 6 months after the end of the PA incentive program.

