### Outcomes

Outcome assessments will be performed after hospital discharge (T0), at 6 months (T1), and at 12 months (T2). The PA therapist will confirm the T1 and T2 medical appointments 3 weeks before the due date to avoid time bias. If the participant cannot attend the medical appointment, it will be delayed for a maximum of 3 days. The same practitioners, a medical doctor and a professional PA therapist will perform all assessments at the University Hospital of Limoges. The clinical examination, test and questionnaires will last around 90 min.

The primary outcome will be the distance walked during the 6MWT, which is widely used in stroke studies [23, 24]. The 6MWT provides an objective measure of functional ability, endurance, and walking ability in people with physical impairments and stroke sequelae [25]. In addition, the 6MWT is a predictor of individual community walking activity, ambulation, and social integration in stroke survivors [26]. Patients will refrain from alcohol, tobacco, and caffeine consumption in the 24 hours before testing. The final score will be the distance walked during the 6MWT, and the rating of perceived exertion, assessed with the modified CR10 Borg scale from 0 to 10, will also be noted at the end of the test [27]. Secondary outcomes with the specific measurements are presented in Fig. 2.

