## Discussion

The aim of the proposed study is to evaluate how a 6-month home-based physical activity incentive and education program affects functional capacity during the subacute phase of stroke recovery. The primary objective of the intervention is to encourage patients to meet PA recommendations and increase their 6MWT distance. The study is therefore designed to determine whether the home-based PA incentive program induces lifestyle changes and increases the amount of PA at medium-term and long-term follow up.

A previous study demonstrated that a home-based education program significantly reduced systolic blood pressure and body mass index, while it improved the distance the patient could walk after 12-month follow up [32]. However, the studied population included patients with transient ischemic attack, and their walking capacity and PA were measured subjectively (deliberate exercise walks). Therefore, to avoid these biases, our proposed study will only include stroke patients, and the protocol will provide objectively measured PA using a body-monitoring device.

Another previous randomized controlled trial showed that a home-based PA program had positive effects on the following: functional capacity, Barthel Index, physical and mental scores in the SF-36 questionnaire, and reduced risk of fracture after 12-month follow up [33]. Furthermore, a randomized controlled trial in a small sample of hemiplegic patients demonstrated that a home-based PA program was feasible, safe, and led to improved 6MWT distance and Timed Up-And-Go (TUG) test time [34]. Additional evidence is required on home-based PA in the subacute phase of stroke recovery.

The main limitation of the study will be the absence of PA monitoring in the control group. However, PA monitoring in the CG could bring about other forms of bias, such as the Hawthorne effect [35], i.e. the presence of a sensor could cause patients to change their lifestyles. Additionally, adherence to PA monitoring is reportedly low in stroke populations with low levels of balance, self-efficacy and walking endurance [36]. Despite this, remote PA monitoring is a common method used to quantify physical activity [14, 37]. Half of the studies in stroke patients have used accelerometers to measure walking or gait skills, and a third of them have used accelerometers to assess upper limb or arm movement [12].

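### The primary 6MWT comparison is not tied to one visit, so either 6 months (T1) or 12 months (T2) could be reported as primary at 5%

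*Protocol article*

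**What the plan says.** All places are in the protocol article.

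- **Background, aims.** The primary aim is the effect on the 6MWT of the "program over 12 months in the subacute phase of stroke recovery". The secondary objective is to assess "whether and how well patients keep practicing PA at 6 months after the end of the PA incentive program", which falls at T2 but concerns physical activity (PA), not walking distance.
- **Study design and settings.** The intervention arm has the programme for 6 months and then 6 months of traditional follow up. The control arm has 12 months of traditional follow up.
- **Outcomes.** Assessments are at T0, T1 (6 months) and T2 (12 months). "The primary outcome will be the distance walked during the 6MWT, which is widely used in stroke studies"; no visit is attached to it.
- **Sample size calculation.** A 30% improvement in 6MWT distance, alpha 5% (two-sided) and power 80% give 36 per group, raised by 15% to 42. No visit is named.
- **Statistical analysis.** The groups are compared on 6MWT distance by a t test or a Mann–Whitney test, with no visit named. Comparisons across T0, T1 and T2 follow. No hierarchy, alpha split or joint rule is given, and a detailed analysis plan is announced.
- **Discussion.** The aim is restated as to "evaluate how a 6-month home-based physical activity incentive and education program affects functional capacity". The study is also to show whether the programme "increases the amount of PA at medium-term and long-term follow up"; the two horizons are not ranked.

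**The concern.** T1 and T2 answer different questions. T1 measures the effect at the end of active coaching. T2 measures what is left after six months without it. A trial sized for one comparison at 5% needs one of them to be the primary contrast.

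The text does give a time frame for the primary aim, but that time frame does not select one of the two post-baseline visits. If the choice is still open when the data are analysed, the headline result can follow whichever visit is significant. The stated 5% would then no longer be the chance of a false positive on the primary outcome.

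**Working it through.** **1. Does any section settle the visit?**

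| Section | Time information on the primary 6MWT comparison |
|---|---|
| Background | over 12 months: T2 alone, or the T0–T1–T2 course |
| Study design and settings | programme ends at 6 months (T1); follow up ends at 12 months (T2) |
| Outcomes | measured at T0, T1 and T2; no primary visit |
| Sample size calculation | none |
| Statistical analysis | none for the between-group test; no order between visits |
| Discussion | length of the programme only; medium and long term not ranked |

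None of them does.

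**2. The plan's own figure.** The inflation reproduces: 36 × 1.15 = 41.4, so 42 per group and 84 in total. The 36 itself does not follow from the stated inputs. With n = 2(1.960 + 0.842)² × SD²/0.30², reading the 30% variance as SD = 0.30 gives 16 per group, and reading it as variance = 0.30 gives 53. That is a separate matter and does not bear on this point. What matters here is that one alpha of 5% was used, with no allowance for a second primary test.

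**3. Error rate if either visit may count as success.** Inputs: two tests, each two-sided at 5% (critical value 1.96), no true effect at either visit, and test statistics that are bivariate normal with correlation ρ. The documents give no T1–T2 correlation, so ρ is an assumption shown as a range.

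Overall error = 1 − P(|Z1| < 1.96 and |Z2| < 1.96)

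| ρ | Overall two-sided type I error | False claim in favour of the programme |
|---|---|---|
| 0.5 | 9.1% | 4.5% |
| 0.7 | 8.4% | 4.2% |
| 0.8 | 7.8% | 3.9% |
| 0.9 | 7.0% | 3.5% |

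A single test gives 5% and 2.5%. The upper bound, for independent tests, is 1 − 0.95² = 9.75%; repeated walking distances in the same patients should be well correlated, so the table is the more realistic range.

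**4. Cost of keeping both visits as primary by splitting alpha.** The standardised effect implied by 36 per group is d = √(2/36) × (1.960 + 0.842) = 0.66. At 2.5% per test the critical value is 2.241.

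- Power with 36 per group: Φ(0.66 × √(36/2) − 2.241) = Φ(0.56), about 71% instead of 80%.
- Number needed for 80%: 2(2.241 + 0.842)²/0.66² ≈ 43.6, so 44 per group before the 15%.

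Naming one visit avoids this cost: the error stays at 5%, and the sample size needs no change on this account.

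**The case against.** **There is no contradiction between two visits.** A reader might infer that the Background says 12 months and the Discussion says 6. The text does not support that. In the Discussion, the 6 months is the length of the programme. A 6-month programme evaluated over 12 months fits the design exactly. This stands: the fault is an unresolved choice.

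**The secondary objective does not make T1 primary.** One might argue that T2 is already taken for persistence, which leaves T1 for the 6MWT. That objective concerns continued PA, a different variable, and a 12-month walking outcome can sit beside it. This also stands; the text gives no ground for preferring T1 over T2.

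**The plan does not declare two primary tests.** The single alpha in the sample size suggests that one contrast was intended. So 7.0% to 9.1% is not the error rate of the plan as written. It is the rate under a reading that the text leaves open. This stands as a condition on the figure.

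**The visit may be fixed elsewhere.** The outcome and timeline figures are not shown, an analysis plan is announced, and an article condenses a fuller protocol. This stands only in part. The visit is part of the definition of the primary outcome and is not a detail that a protocol article commonly leaves out. The 30% effect and the 5% alpha have a clear meaning only for a named contrast. The article also goes beyond silence: it states a time frame that does not identify the visit. If the full protocol already names one, the fix is to carry it into these sections.

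**Conclusion.** The point holds as an unnamed primary visit. The aim, the outcome, the effect size, the alpha and the between-group test are tied to neither T1 nor T2, and no order between them is stated. As the text stands, either visit could be reported as the primary result at 5%.

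The overall type I error would be about 7.0% to 9.1% instead of 5%. This rests on two assumptions: both visits are tested at two-sided 5% with either counting as success, and the test statistics correlate between 0.9 and 0.5.

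It would go too far to say that the article sets two conflicting primary visits, that inflation has been shown to occur, or that T1 is the right choice. Trial status reports 50 of 84 patients enrolled, so recruitment was still open and the matter could be settled before the data are analysed.

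**What to change.** Before database lock, and before any between-group result is seen:

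1. Name one visit, T1 or T2, whichever the sponsor's original aim intends, for the primary between-group difference in 6MWT distance. Adjust it for the T0 distance, which is already collected. Record the date of the decision.
2. Make the 6MWT difference at the other visit the key secondary, tested at 5% only if the primary is significant. With this fixed order, the two 6MWT claims together stay within 5%.
3. Align the primary aim in the Background with the Outcomes, Sample size calculation and Statistical analysis sections, and carry the same wording into the analysis plan. State that the 30% effect refers to the named visit.

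The cost is wording only: no extra patients, visits or measurements. The one real downside is that the second visit cannot rescue a negative primary result. The T0 adjustment is good practice for this contrast and is not what cures the ambiguity; naming the visit does that.

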## Methods

### Ethics approval and considerations

All procedures will follow the recommendations of the institutional ethical committees per the Good Clinical Practice Guidelines of the Declaration of Helsinki. This project received authorization from the ethics and individual protection committee (IPC) (RCB: 2012-A01456-37) and is registered at http://ClinicalTrials.gov (NCT01822938). The Standard Protocol Items: Recommendations for Interventional Trials (SPIRIT) checklist is available as Additional file 1.

### Study design and settings

Ticaa’dom is a comparative prospective, observer-blinded, monocentric, parallel, randomized controlled clinical trial. The Neurological and Physical Medicine and Rehabilitation Services of Limoges University will conduct this study in the Limousin region of France.

Ticaa’dom will also include a home-based 12-month post-discharge study conducted by professional PA therapists. The protocol will include two groups: the home-based physical activity incentive group (HB-PAI) and the control group (CG). The HB-PAI will include a physical activity incentive and education program for the first 6 months, followed by 6 months of traditional follow up. The CG will receive traditional follow up for 12 months (Fig. 1).

**Fig. 1 Fig1:**
[figure not shown]
Study flow chart. *CG* control group, *HB-PAI* home-based physical activity incentive group

### Participants

Prior to hospital discharge, physicians will inform the patients of the purpose and methods of the study. The inclusion criteria will be the following: age ≥18 years; recovery from first ischemic or hemorrhagic stroke in all brain areas; stroke within <6 months; Functional Ambulation Classification score ≥2; patient monitoring by the post stroke interventional mobile team (HEMIPASS); and registration with the French social security system.

The exclusion criteria for both groups will be the following: stroke recurrence; disorders limiting gait skills before or after stroke; cognitive disorders impeding comprehension of physical activity education i.e. aphasia indicated by a Boston Diagnostic Aphasia Examination (BDAE) score <2; non-controlled hypertension; inability to complete questionnaires; cardiopulmonary pathology preventing effort completion; non-signature of written consent; involvement in other research; legal guardianship; and pregnancy.

### Intervention

#### Physical activity incentive and education program

The PA therapist will design and implement the PA incentive program for each participant. The program will include two phases: education and incentive. In the education phase, the therapist will explain the benefits of a regular physical activity practice. PA education will follow the recommendations of the French Society of Physical Medicine and Rehabilitation (SOFMER) and the French Neurovascular Society (SFNV) and will include educational diagnosis, selection of physical activities, and definition of goals [22].

The incentive phase will include monitoring, weekly telephone calls, and a home visit every 3 weeks for 6 months. A SenseWear armband accelerometer (BodyMedia, Pittsburgh, PA, USA) will be used to measure PA at home. The participant will wear the device during the daytime and remove it at night. The investigators will analyze the PA monitoring in three different categories: frequency (SC per week), PA duration, and PA intensity (TEE above 3 metabolic equivalents (METs)). The participant will complete a simple chart every day to measure subjective perception of PA for the physicians to compare the subjective and real amount and intensity of PA. The patients will receive a phone call once a week to encourage regular PA and to inquire about the PA measuring device. The PA therapist and HEMIPASS will perform a home visit every 3 weeks to discuss PA parameters – i.e. SC, TEE and physical activity duration – to incite regular practice, and to set objectives for the next visit.

### Control group

The CG will receive traditional follow up, including a medical appointment at 1 and 6 months after the hospital discharge. The CG will not monitor their PA and will not receive home visits or telephone calls. After inclusion, the PA therapist will give an explanation of PA recommendations and the benefits of an active lifestyle on stroke recurrence prevention.

The Ticaa’dom protocol is a strategy to monitor and incite PA at home in stroke survivors. In this context, ambulatory care in stroke rehabilitation – i.e. physiotherapy – will be authorized during the trial for both groups. In contrast, intensive after-discharge rehabilitation programs conducted by the hospital’s rehabilitation service or participation in other PA programs will not be allowed during the experiment. If hospital rehabilitation is mandatory, the participant will be excluded from the study.

### Outcomes

Outcome assessments will be performed after hospital discharge (T0), at 6 months (T1), and at 12 months (T2). The PA therapist will confirm the T1 and T2 medical appointments 3 weeks before the due date to avoid time bias. If the participant cannot attend the medical appointment, it will be delayed for a maximum of 3 days. The same practitioners, a medical doctor and a professional PA therapist will perform all assessments at the University Hospital of Limoges. The clinical examination, test and questionnaires will last around 90 min.

The primary outcome will be the distance walked during the 6MWT, which is widely used in stroke studies [23, 24]. The 6MWT provides an objective measure of functional ability, endurance, and walking ability in people with physical impairments and stroke sequelae [25]. In addition, the 6MWT is a predictor of individual community walking activity, ambulation, and social integration in stroke survivors [26]. Patients will refrain from alcohol, tobacco, and caffeine consumption in the 24 hours before testing. The final score will be the distance walked during the 6MWT, and the rating of perceived exertion, assessed with the modified CR10 Borg scale from 0 to 10, will also be noted at the end of the test [27]. Secondary outcomes with the specific measurements are presented in Fig. 2.

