### Sample size calculation

The Biostatistics unit of the Limoges University has calculated the sample size using the Nquery Advisor software (Version 6.1). The calculation is based on previous studies according to the protocol similarities in the home-based setting and protocol outcomes [31]. We hypothesized that the PA incentive program would improve the 6MWT distance by 30%. We have performed bilateral estimation with variance of 30%, alpha risk of 5% and power of 80%. The resulting required sample size was 36 subjects per group. We added 15% to ensure the statistical power of the study. As a result, the total sample will be 84 patients: 42 in the HB-PAI and 42 in the CG group (Fig. 4).

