### Interruption and exclusion conditions

Authors will be empowered to remove any participant in the case of stroke relapse, serious adverse event, participant desire to withdraw, or development of any other condition impeding the participant’s independent movement. Patients who die will not be included in the analysis; patients who withdraw consent will be excluded from the study.

If the participant is absent at the evaluation or clinical examination, they will be excluded from the study, and will be followed up to determine the cause of the absence. We will take missing data into consideration by the last observation carried forward (LOCF) strategy. The PA therapist will document all withdrawals on the CRF along with the supplementary clinical information. A 15-day maximum period of pause will be tolerated.

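### The 3-day limit on late T1 and T2 visits, read with the exclusion-for-absence rule, can cost an obtainable primary 6MWT; the protocol should say what happens after day 3

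*Protocol article*

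**What the plan says.** The Outcomes section schedules assessments after discharge (T0), at 6 months (T1) and at 12 months (T2), and names the endpoint: "The primary outcome will be the distance walked during the 6MWT". Two sentences govern timing. The first is a precaution: "The PA therapist will confirm the T1 and T2 medical appointments 3 weeks before the due date to avoid time bias". The second is the limit: "If the participant cannot attend the medical appointment, it will be delayed for a maximum of 3 days". No route is described for a visit after that limit.

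Interruption and exclusion conditions gives the consequence of not attending: "If the participant is absent at the evaluation or clinical examination, they will be excluded from the study". It adds the missing-data rule: "We will take missing data into consideration by the last observation carried forward (LOCF) strategy". It ends with a further time limit: "A 15-day maximum period of pause will be tolerated". What may be paused is not stated.

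Sample size calculation requires 36 per group and describes its reserve as follows: "We added 15% to ensure the statistical power of the study". This gives 42 per group.

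**The concern.** Three days is a short tolerance for visits six months apart. All assessments take place at one hospital with the same assessors, and participants may enter with a Functional Ambulation Classification score as low as 2. A week's illness or a transport problem is enough to miss the limit.

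The limit alone would be harmless if a late participant were simply tested late. The difficulty is its combination with the absence rule. Someone not seen by day 3 can be counted as absent and excluded, or have an earlier distance carried forward. Either way the trial loses a measurement of its primary endpoint that it could have had.

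The participants most likely to be lost this way are plausibly the less well and less mobile, whose walking distance differs from the rest. Until T1 the intervention arm has weekly calls and home visits every three weeks, and the control arm has neither, so rebooking may be easier in one arm than in the other.

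**Working it through.** **1. Inputs.** From the article: a 3-day limit, a 15-day pause, visits 6 months apart (taken as 183 days), 36 required and 42 recruited per group, two-sided alpha 5%, power 80%. Assumed: roughly linear change in 6MWT distance between visits, a 6-month change of 10% to 30%, and 2% to 8% of participants missing the limit at each visit.

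**2. The plan's reserve.** 36 × 1.15 = 41.4, rounded up to 42, so the inflation step reproduces. The reserve is 42 − 36 = 6 per arm. The 36 is taken as given here, although it does not follow from the stated effect and variance; that is a separate matter.

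**3. The two limits against the interval.** 3/183 = 1.6% and 15/183 = 8.2%. If the pause covers attendance at assessments, a pause that starts on the due date could overrun the visit limit by 15 − 3 = 12 days. If it covers only the programme, there is no overrun.

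**4. Cost of a late test against cost of a lost one.**
- Tested 14 days late: 14/183 = 7.7% of the 6-month change is misplaced. For a change of 10% to 30% this is 0.077 × 10% = 0.8% to 0.077 × 30% = 2.3% of the starting distance.
- Not tested at T1, T0 carried forward: 100% of the change is erased, that is 10% to 30% of the starting distance.
- Ratio: 183/14 = about 13.

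**5. How many could be affected.** With p the chance of missing the limit at one visit, the expected number per arm is 42p at one visit and 42 × [1 − (1 − p)²] missing at least one of two, if misses are independent.

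| p (assumed) | One visit | At least one of two |
|---|---|---|
| 2% | 0.8 | 3.96% → 1.7 |
| 5% | 2.1 | 9.75% → 4.1 |
| 8% | 3.4 | 15.4% → 6.5 |

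The two-visit column matters for a single analysis only if a miss at T1 also removes the participant at T2, as exclusion would do.

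**6. Effect on power if these participants are removed.** With 36 per group, 80% power corresponds to a standardized difference of about 0.67. At that difference, power is 85.8% with no loss from 42, 84.0% with 5% loss, 81.9% with 10%, 80.0% with 14.3% (36 left), 79.7% with 15% and 77.2% with 20%. Missing one visit at 2% to 8% therefore keeps power above 80% from this cause alone. The same 6 places must also cover deaths, withdrawals, recurrences and mandatory rehabilitation.

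**The case against.** A narrow window is a legitimate way to limit time bias, and the three-week confirmation applies to both arms and should reduce missed visits. That stands. It does not explain why someone who still misses the limit should go unmeasured.

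A reader might infer that late 6MWT values are thrown away. The article does not say so. It describes no test after day 3 at all, and the exposure arises only through the absence rule. Handling of out-of-window values may also be set out in the analysis plan that the article announces. However, the absence rule is stated in the article itself, and analysis rules cannot recover a test that was never performed.

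A reader might also infer that the 3-day and 15-day limits contradict each other. This is not shown. The pause is undefined and may concern only the programme. On that reading it would not bear on controls, who have no programme, or on T2, which falls after the programme ends. It is an undefined term that needs defining.

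The argument about unequal loss is limited too. After 6 months both arms receive traditional follow-up, so it applies mainly at T1, where controls also have a scheduled 6-month appointment.

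Finally, a symmetric wider window would be a poor remedy, because it would allow T1 testing before the 6-month programme is complete. This objection stands and shapes the fix.

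**Conclusion.** The concern holds in a limited form. Followed as written, the visit limit and the absence rule together expose a participant who can attend only after day 3 to exclusion or to LOCF, and a primary measurement that could have been obtained is lost. The article does not say which of the two consequences applies.

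For an individual, the loss is far larger than the timing error avoided: the whole 6-month change under LOCF from T0 to T1, against about 7.7% of it for a test two weeks late. That comparison rests on linear change. The number of participants affected cannot be derived from the documents. The range of 0.8 to 3.4 per arm at one visit, or up to 6.5 across two, is purely illustrative. Only its upper end over two visits would use up the reserve of 6. This is a worthwhile, inexpensive improvement, not a flaw that threatens the trial.

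**What to change.** Keep the due date plus 3 days as the target. Add that a participant who misses it is still assessed as soon as possible, that the actual date is recorded, and that the value is kept in the primary analysis. Add a sensitivity analysis restricted to in-target tests. Any wider window at T1 should extend later only, so that no test precedes the end of the 6-month programme.

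Reconcile Outcomes with Interruption and exclusion conditions: state what happens to a participant after day 3, and say what the 15-day pause covers and whether it affects visit timing. Lateness at one visit should not by itself remove a randomized participant from the analysis.

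The cost is a few sentences and slightly more spread in assessment times, which the recorded dates allow the analysis to examine. With 50 of 84 already enrolled, some visits may have taken place under the tighter rule. The date of the change should therefore be documented.
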